## Abstract

**Background:**

Schema Therapy (ST) is an integrative psychotherapy based upon a cognitive schema model which aims at identifying and changing dysfunctional schemas and modes through cognitive, experiential and behavioral pathways. It is specifically developed for patients with personality disorders. Its effectiveness and efficiency have been demonstrated in a few randomized controlled trials, but ST has not been evaluated in regular mental healthcare settings. This paper describes the study protocol of a multisite randomized 2-group design, aimed at evaluating the implementation of outpatient schema therapy for patients with borderline personality disorder (BPD) in regular mental healthcare and at determining the added value of therapist telephone availability outside office hours in case of crisis.

**Methods/Design:**

Patient outcome measures will be assessed with a semi-structured interview and self-report measures on BPD, therapeutic alliance, quality of life, costs and general psychopathology at baseline, 6, 12, 18 and 36 months. Intention-to-treat analyses will be executed with survival analysis for dichotomous variables, and one-sample t-tests and ANCOVAs for continuous variables with baseline as covariate and condition as between group factor. All tests will be two-tailed with a significance level of 5%.

**Discussion:**

The study will provide an answer to the question whether ST can be effectively implemented and whether phone support by the therapist has an additional value.

**Trial Registration:**

The Dutch Cochrane Center, NTR (TC = 1781).

## Background

Borderline Personality Disorder (BPD) is a disabling psychiatric disorder, which is characterized by substantial distress and disruptions in functioning. It has for long been viewed as a severe and difficult to treat psychiatric condition. However, during recent years several promising treatment possibilities have been developed. Among them, Schema Therapy (ST) was found to be effective regarding all aspects of BPD [1,2]. How well ST can be delivered in regular mental healthcare practice is unknown, but it is expected that its implementation poses challenges.

BPD is marked by chronic instability in multiple areas (emotional dysregulation, self-harm, impulsivity and identity disturbance). The lifetime prevalence of BPD in the general population is 1-2%. In psychiatric outpatient settings 10% of the patients suffer from BPD, in psychiatric inpatients settings 20% [3]. The medical and societal costs for BPD are substantial [2,4,5]. About 10% of the BPD patients die because of suicide [6,7].

However, recent years showed progress in the development of treatment options [8-14] that are supported by randomized controlled trials [1,7,15-19]. These treatments demonstrated effectiveness on symptom level, as manifested by reduced suicide attempts, fewer acts of self-harm or hospitalizations. Although pharmacological treatment can reduce symptoms, a Cochrane review indicates that there is no convincing evidence that any medication has complete success [20]. Psychotherapy is the necessary and primary treatment modality for BPD [21]. In a RCT which compared Schema Therapy and Transference Focused Psychotherapy (TFP) [1] both therapies showed a significant change in patients' personality, also at 1-year follow up [22]. This study showed that three years of ST and TFP proved to bring about a significant change in patient's personality, shown by reductions in all BPD symptoms and general psychopathologic dysfunction, increases in quality of life, and changes in associated personality features. While both treatment conditions showed positive results in the treatment of many aspects of BPD, ST was superior to TFP with respect to reduction in BPD manifestations, general psychopathologic dysfunction, and change in ST/TFP personality concepts. ST had a recovery rate of 45.5% and a reliable change rate of 65.9% at three years, whereas the dropout rate for ST (27%) was significantly lower than for TFP (51%). As a result of these findings, ST is considered as an evidence based treatment option for borderline personality disorder in the Multidisciplinary Dutch Guidelines on Personality Disorders [23].

Based on these positive results, a study of the implementation of ST in regular mental healthcare practice was planned. The rationale is that clinical interventions with proven effectiveness are not necessarily implemented in regular practice and, if implemented, treatment outcomes are not always equally good as in the clinical trial. One of the premises in the therapeutic approach of ST [11,13,14] and Dialectical Behavior Therapy [8,9,17,18] is that borderline patients need extra support of the therapist in between sessions when they are in crisis or in emotional need. For this reason patients are offered a special phone number where they can reach their therapist outside office hours. This personal connection between sessions is suggested to help to refute the patient's beliefs that there is nobody who really cares and can help to prevent or overcome crisis. In a pilot study of ST crisis support in the form of therapist phone accessibility outside office hours was one of the most controversial topics [24] and led some therapists to withdraw from the project. In general mental healthcare there is much discussion about this topic because of the financial consequences, the burden to and responsibility of the therapist, and the possible risk of violation of boundaries. Therefore, telephone accessibility outside office hours was perceived as an important barrier for the successful implementation of ST in regular practice. The RCT by Giesen-Bloo et al. [1] demonstrated that ST is a successful treatment, but it remains unknown whether the crisis support by the therapist was crucial to outcomes. Since the issue of crisis support outside office hours by the therapist makes it difficult to implement ST in regular practice and its effect has never been examined, we decided to investigate the role of the crisis support outside office hours in the implementation study by randomly allocating the crisis support outside office hours to 50% of the therapists.

In sum, this study will test the implementation of ST for BPD in regular mental healthcare and will compare two modalities: one with extra crisis support by the therapist outside office hours and one without such telephone support. The study has three aims. First, to assess whether patient outcomes after 1.5 years of ST will be the same when implemented in regular practice, compared to what was found in the RCT [1]. Since rigorous evaluations such as RCTs always imply controlled conditions, it is unclear to what extent their positive effects can be generalized to regular clinical practice. Treatment effects may be more modest outside RCTs because of different circumstances [25-27]. The second aim will be to assess the added value of therapist telephone availability outside office hours in case of crisis (TTA) during the 1.5 yrs of ST. The third aim will be to assess the problems that may arise during the implementation process.

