#### Training and supervision

As the primary aim of the study is to assess whether ST can be successfully implemented in regular mental healthcare practice, we will make the following adjustments compared to the Giesen-Bloo et al. trial. In the study of Giesen-Bloo et al. [1] the ST therapists were trained and supervised by the originator of ST, Jeffrey Young, in the implementation study the therapists will be trained and supervised by Dutch experts [55,56]. The training will be based on a structured and piloted program supported by a set of DVDs with examples of ST techniques, see Nadort et al. [54].

Therapists will be trained in a 50 hours training program (eight days during a period of two months). Essential to the treatment is expert supervision and peer supervision. During the first year monthly supervision will be provided on each site, in the second year supervision will be provided every two months. The therapists will have weekly peer supervision on each site. There will be a 1-day central supervision for all therapists once a year.

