### Analysis

The statistical analyses will be based on the intention-to-treat as randomized principle. Treatment effects will be tested with survival analysis for dichotomous variables, and one-sample t-tests and ANCOVAs for continuous variables with baseline as covariate and condition as between group factor. When no deviations from distributional assumptions are detected, parametric ANCOVAs will be used.

Using Cohen's formula, effect sizes will be calculated as X_1_-X_2_/SD_pooled_, were X_1 _represents the pre-treatment scores, X_2 _the post-treatment scores, and SD_pooled _represents the pooled standard deviations of the pre- and post-treatment scores.

All the tests will be two-tailed with a significance level of 5%. Analyses will be performed using the Statistical Package for Social Sciences, version 15.0 for Windows (survival analyses, within-group analyses, Chi-square tests).

In the RCT [1] a pre to post treatment effect size difference of d = 1.24 (Cohen's d) was found on the main patient outcome measure BPDSI on 18 months. In the present study, the same treatment will be less intensive and executed in non-academic practice, so that a lower effectiveness can be expected. We therefore tentatively estimate the pre-post difference as d = 1.0.

It will be concluded that extra crisis support is definitely helpful if at the patient level a medium effect difference is found between the conditions with and without extra phone support. A possible small difference in effect will, although indicating that the extra support is helpful, probably not convince clinicians to implement this extra availability in their regular practice.

For the economic evaluation, analysis will also be performed according to intention-to-treat principle. The uncertainty around the cost-effectiveness and cost-utility ratios will be analyzed using bootstrapping techniques. Results of these bootstraps will be presented in cost-effectiveness planes

(showing all bootstrapped cost-effectiveness combinations) and cost-effectiveness acceptability curves (CEACs) which represent the probability that the intervention is cost-effective, given a certain threshold for the costs per unit of effect gained.

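### Aim 1 asks whether outcomes match those of the earlier RCT, but the one-sample t-test that the plan names cannot answer this, whatever its reference value

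*Protocol article*

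**What the plan says.** The Background lists three aims. The first is "to assess whether patient outcomes after 1.5 years of ST will be the same when implemented in regular practice", set against the earlier RCT of ST. Study Design repeats it as a comparison of routine-care results with those of a randomised trial in academic settings. Training and supervision says that "the primary aim of the study is to assess whether ST can be successfully implemented in regular mental healthcare practice".

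The Analysis section states: "Treatment effects will be tested with survival analysis for dichotomous variables, and one-sample t-tests and ANCOVAs for continuous variables". ANCOVA has baseline as covariate and condition as factor. All tests are two-tailed at 5%. The section gives no reference value for the one-sample t-test.

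Later in the same section the RCT result appears as a "pre to post treatment effect size difference of d = 1.24" at 18 months, with no standard error, interval or sample size. Less intensive treatment in non-academic practice is expected to do less well: "We therefore tentatively estimate the pre-post difference as d = 1.0".

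The only decision rule concerns therapist telephone availability (TTA): "It will be concluded that extra crisis support is definitely helpful if at the patient level a medium effect difference is found". The only power calculation, under Sample size, is also for TTA.

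On crisis support in the RCT, the Background says "it remains unknown whether the crisis support by the therapist was crucial to outcomes", which treats it as part of the treatment given there. Under Randomization, half of the therapists here work without it.

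**The concern.** The aim and the test do not match. The aim is a comparison between two studies, phrased as sameness. The tests are difference tests within one study. Since the ANCOVA contrasts TTA with no TTA, the one-sample t-test is the only continuous-outcome test left that could address the RCT.

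The conclusion on implementation could then fail in several ways. A highly significant pre-post change could stand in for an answer although it says nothing about the RCT. A real shortfall could go undetected because the sample is small. Or routine care could be declared worse because the RCT figure was itself imprecise. If both conditions are pooled, a shortfall could also reflect the absence of TTA in half the sample, not the setting.

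**Working it through.** **The plan's own figure.** None is given for aim 1. The stated power of 84 under Sample size concerns the TTA contrast and plays no part here.

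**Inputs from the protocol.** RCT d = 1.24 and expected d = 1.0 (Analysis), so the gap is 0.24. Minimum of 60 patients (Sample size). Two-tailed alpha 0.05 (Analysis). d is mean change divided by the pooled pre-post SD (Analysis).

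**Assumptions.**
- Pre-post correlation r = 0.3, 0.5 or 0.7, the same in both studies. The SD of change in pooled-SD units is then √(2(1−r)) = 1.183, 1.000 or 0.775.
- RCT ST arm of 44. The Background gives 45.5% recovered, 65.9% reliably changed and 27% dropout, and 20/44, 29/44 and 12/44 fit all three. The next size that fits is 88. A range of 30 to 60 is shown.
- The pooled SD is treated as known throughout. There is no dropout and no clustering by therapist.

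**Reading 1: reference value zero.** With a true d of 1.0 and n = 60, power is about 100% at every r. The result confirms that patients improve and carries no information about the RCT.

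**Reading 2: reference value 1.24.**

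*Chance of missing the expected shortfall.* The noncentrality is 0.24·√60 / √(2(1−r)) on 59 degrees of freedom.

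| r | noncentrality | power | missed |
|---|---|---|---|
| 0.3 | 1.57 | 34% | 66% |
| 0.5 | 1.86 | 45% | 55% |
| 0.7 | 2.40 | 66% | 34% |

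*Precision of the benchmark.* With 44 patients the 95% half-width around 1.24 is 1.96·√(2(1−r))/√44 = 0.35, 0.30 or 0.23. That is about as large as the 0.24 gap or larger.

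*True error rate if 1.24 is treated as fixed.* With no true difference between studies, the standard error of the difference exceeds the one used by √(1 + 60/n_RCT), and r cancels. The error is 2·(1 − Φ(1.96/√(1 + 60/n_RCT))):
- n_RCT = 30: ratio 1.732, error 26%
- n_RCT = 44: ratio 1.537, error 20%
- n_RCT = 60: ratio 1.414, error 17%

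Even at 88 it would be about 13%.

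**If the conditions are pooled.** Taking the planning value of 0.5 for TTA and half the patients without it, the pooled d falls by 0.5 × 0.5 = 0.25. That is about the whole 0.24 gap, which the Analysis section attributes to intensity and setting. This puts a between-condition d on the pre-post scale, so it is only an illustration.

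**What a proper comparison would deliver.** The 95% half-width for the difference is 1.96·√(2(1−r))·√(1/60 + 1/44) = 0.46, 0.39 or 0.30 for r = 0.3, 0.5 or 0.7. For the TTA condition alone (30 against 44) it is 0.55, 0.46 or 0.36.

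**The case against.** The strongest reply is that the plan never says the t-test is run against 1.24. The software sentence mentions within-group analyses, which suits a test of change against zero, and 1.24 appears only as the basis for expecting 1.0. This is correct, and the figures under Reading 2 apply only if that reading is meant. It does not rescue the plan, because under the other reading aim 1 has no continuous-outcome test at all.

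A reader might also infer that a non-significant result is going to be reported as sameness. The document does not say so. Strengths and limitations states the opposite principle for TTA: failing to find a difference does not establish equivalence. The Background and Analysis openly allow for a smaller effect. The principle is simply not carried over to aim 1.

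Nor does the document say that the two conditions are pooled for aim 1, so the mixing of setting with TTA is conditional. The 0.5 was adopted because the TTA effect is unknown.

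The missing margin and reference value could be details that a condensed article leaves to the full protocol or analysis plan. Taken alone, they would be no finding. What stands is that the method actually named does not fit the aim.

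Finally, calling successful implementation primary covers delivery and process as well as outcome, so it should not be equated with sameness to the RCT.

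**Conclusion.** The point holds in this form: the plan's one-sample t-test cannot answer aim 1 under either possible reference value. Against zero it does not address the RCT. Against 1.24 it would have a true two-sided error of about 20% (26% to 17% for an RCT arm of 30 to 60) and would miss the plan's own expected shortfall 34% to 66% of the time. In neither case could it show sameness.

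These sizes rest on the assumed correlation, the inferred RCT arm, a known pooled SD, no dropout and no therapist clustering. Allowing for error in the SD would widen the intervals further. Mixing with TTA is a further problem only if the conditions are pooled.

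The documents do not support saying that the plan tests against 1.24, that it will read p > 0.05 as sameness, or that 0.5 SD is its margin for aim 1. The randomised TTA comparison is not affected by this point.

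**What to change.** State that aim 1 is answered by the difference in 18-month BPDSI-IV pre-post change between this study and the RCT's ST arm, with a 95% confidence interval built from both studies' standard errors. Keep the one-sample test against zero, if wanted, as a description of within-study change only. State that sameness is not concluded from p > 0.05 and that a wide interval is reported as inconclusive.

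Report the TTA condition against the RCT as well as the whole sample, and note that trainers, session frequency and setting still differ, so neither comparison isolates setting.

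Any claim of 'not worse' needs a margin that the sponsor justifies and states before results are seen. The 0.5 SD threshold should not be adopted by default. It was set as a worthwhile TTA benefit, and as a tolerable loss it would give up 0.5/1.24 = 40% of the RCT effect.

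The change needs no new patients or assessments, but it does need the RCT arm's means, SDs and sample size. The cost is wider intervals, and aim 1 may well end inconclusive. For illustration only, even a margin of 0.5 (one-sided 2.5%, 60 against 44) would be met 57%, 71% or 90% of the time if the studies are truly equal (r = 0.3, 0.5, 0.7). If the true gap is 0.24, it would be met 20%, 26% or 39% of the time. This should be acknowledged in advance.

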## Methods/Design

### Study Design

This study is a multicenter randomized two-group trial for studying the added value of therapists phone support outside office hours. It is also a clinical evaluation of implementing ST for BPD and a comparison of the regular mental healthcare treatment results with those in a randomized clinical trial in academic settings. The interventions and assessments will be executed between December 2005 and August 2010.

### Recruitment/Settings and locations

#### Mental healthcare centers

Different mental healthcare centers, covering urbanized areas and located in various parts of the Netherlands will be approached and invited to take part in the implementation study. Selection criteria are a) at least two therapists on each location so that peer supervision groups can be formed, b) therapists agree in executing the telephone availability outside office hours and managers have to give their permission to do so, c) both therapists and managers have to agree in making the necessary time reservations for monthly supervision and weekly peer supervision.

#### Patients and procedures

Patients will be recruited within the departments of the mental healthcare centers. They can also be referred by therapists of other mental health institutes, primary care physicians or psychotherapists with private practices. Patients have to be referred based on a clinical diagnosis of BPD. At each site patients will be screened on the inclusion-exclusion criteria by specialized trained research assistants and be informed about the study. A positive screening procedure takes two months, and this interval serves as a patient's motivational check for undergoing intensive psychotherapy.

If patients are willing and eligible to participate signed informed consent will be obtained after full explanation of the procedures and both conditions of ST at the first assessment and before randomization. See Figure 1 for the flowchart. Participants do not receive compensation for screening or assessments. Participating in assessments is obligatory to receiving the studied treatments.

**Figure 1 F1:**
[figure not shown]
**Shows the procedures in a flow chart**.

### Participants

#### Inclusion criteria

Patients (aged 18-60) are eligible to participate if their main diagnosis is a Borderline Personality Disorder according to the DSM-IV criteria [3]. The Structured Clinical Interview for the Diagnostic and Statistical Manual of Mental Disorders, Fourth Edition (SCID-II) [28,29] will be used for assessing the diagnosis BPD. In addition, the level of symptom severity should be ≥ 20 on the Borderline Personality Disorder Severity Index (BPDSI-IV) [30,31]. Co morbid axis-I and axis-II disorders are allowed as is medication use.

#### Exclusion criteria

Patients are excluded from the study if they suffer from one or more of the following disorders: a psychotic disorder (except short, reactive psychotic episodes), bipolar disorder, dissociative identity disorder, antisocial personality disorder, attention deficit hyperactivity disorder, addiction of such severity that clinical detoxification is indicated (after which entering treatment is possible), psychiatric disorders secondary to medical conditions and mental retardation or if they do not have sufficient command of the Dutch language necessary to participate in the study.

#### Randomization

To prevent regional influences and enhance implementation TTA has to be equally spread over the different sites. Therefore a stratified randomization procedure will be used. The stratification procedure will be performed by a study-independent person and will be concealed for participating therapists, patients and researchers. Stratified per center, 50% of the therapists will be randomly allocated to the condition with extra phone support and 50% of the therapists to the condition without extra phone support. Each therapist will treat two patients either with or without phone support dependent upon the randomization. After completing the baseline assessment and signing the informed consent form patients will be randomly assigned to one of therapists of the participating institutes in their regions.

#### Assessments

Data are collected at four points in time: at baseline (T0), after 6 months of treatment (T1), 12 months of treatment (T2) eighteen months of treatment (T3) and a three- year follow-up (T4). Experienced research assistants with higher vocational training in psychology will be trained on the different sites in assessing patients for treatment outcome measures. Study researchers, screeners, research assistants and therapists are masked to treatment allocation during the screening period and the first assessment.

Table 1 summarizes the measures that are used at each point.

**Table 1 T1:** Summary of measures

**Measure**	**Baseline**	**6 months**	**12 months**	**18 months**	**Follow-up 36 months**
